## Abstract

**Introduction:**

A diagnosis of melanoma in situ presents negligible risk to a person’s lifespan or physical well-being, but existing terminology makes it difficult for patients to distinguish these from higher risk invasive melanomas. This study aims to explore whether using an alternative label for melanoma in situ may influence patients’ management choices and anxiety levels.

**Methods and analysis:**

This study is a between-subjects randomised online experiment, using hypothetical scenarios. Following consent, eligible participants will be randomised 1:1:1 to three labels: ‘melanoma in situ’ (control), ‘low-risk melanocytic neoplasm’ (intervention 1) and ‘low-risk melanocytic neoplasm, in situ’ (intervention 2). The required sample size is 1668 people. The co-primary outcomes are (1) choice between no further surgery or further surgery to ensure clear histological margins greater than 5 mm and (2) choice between patient-initiated clinical follow-up when needed (patient-led surveillance) and regular routinely scheduled clinical follow-up (clinician-led surveillance). Secondary outcomes include diagnosis anxiety, perceived risk of invasive melanoma and of dying from melanoma and management choice anxiety (after surgery choice and follow-up choice). We will make pairwise comparisons across the three diagnostic label groups using regression models (univariable and multivariable).

**Ethics and dissemination:**

The study has been registered with the Australian New Zealand Clinical Trials Registry (ACTRN12624000740594). Ethics approval has been received from The University of Sydney Human Research Ethics Committee (2024/HE000019). The results of the study will be published in a peer-reviewed medical journal, and a plain language summary of the findings will be shared on the Wiser Healthcare publication page (https://www.wiserhealthcare.org.au/category/publications/).

**Trial registration number:**

Australian New Zealand Clinical Trials Registry (ID 386943).

STRENGTHS AND LIMITATIONS OF THIS STUDYThe randomised design enables robust comparison of diagnostic labels on decision-making and psychological outcomes.The study has been co-designed with patients, members of the public and clinicians to ensure that labels and evidence are relevant to end-users.The large online randomised study is representative of adults in the Australian community.The study’s hypothetical nature limits its ability to capture real patients after an actual melanoma in situ diagnosis (or alternative label).The study does not explore the potential for recalibration of diagnostic thresholds using existing labels, the impact of diagnostic labels on actual patient or clinician decisions or the impact of detailed risk information on diagnostic labels, all of which are areas for future research.

## Introduction

 Melanoma incidence and mortality trajectories in Australia and other countries show a classic epidemiological signature of overdiagnosis:^1^ steeply increasing incidence curves coupled with flat mortality trends.^2^,^6^ While ageing populations may lead to a small real increase in melanoma incidence,^7^ much of the increase is likely overdiagnosis.^2^,^6^ This appears to be largely driven by increased diagnosis of melanoma in situ,^2 4 8^ which in Australia is now diagnosed over twice as frequently as invasive melanoma.^9^ Similar findings have been found for melanoma in the USA (diagnosed at least as frequently as invasive melanoma)^3^ and Denmark (diagnosed over half as frequently as invasive melanoma).^10^

Multiple evidence lines indicate that melanoma in situ is a risk factor for invasive melanoma rather than an obligate precursor.^3 9 11 12^ Overdiagnosis is partly driven by lowering the diagnostic threshold over the years, such that the same lesion that was called benign in the past would now be labelled melanoma in situ.^12^ Concerns about litigation may also be driving a tendency to interpret melanocytic lesions as a more severe diagnosis^13^ particularly in partial biopsies or where the lesion extends to the surgical margins. Harms stemming from melanoma overdiagnosis include physical, psychosocial and economic dimensions.^14^ Physical harms can include overtreatment, repeat skin biopsies,^15^ scarring,^15^ pain, infection and/or functional impairment. Psychological harms include anxiety and fear,^16 17^ with many patients perceiving that they have a high risk of dying from melanoma, when their actual risk is much lower (and risk all-cause mortality is actually lower than the population average).^18^ These psychological harms can manifest as anxiety about being outdoors, fear of cancer recurrence, or guilt for past ultraviolet (UV) radiation exposure causing melanoma.^5^ Social harms include impacts of the diagnosis on loved ones, and on patients’ social networks.^15^ Economic harms include treatment costs for the immediate diagnosis and for future long-term clinical surveillance. These incur substantial financial costs to both the health system and patient (as out-of-pocket costs), as well as opportunity costs for both clinician time and patient time. There is also a possible denial of life insurance as the person is now identified as a cancer survivor by many insurance companies.^3^

One possible solution is to consider a new label for melanoma in situ without the word ‘melanoma’.^12^ This might help patients recognise the lower risk of this type of lesion^18^ and help to reduce the potential psychological harm. It may also pave the way for the de-escalation of treatment^19^ and surveillance.^20^,^22^ Evidence from other cancer contexts, including thyroid,^23^ breast^24^ and prostate^25^ lesions, suggests that new diagnostic labels may beneficially impact psychological outcomes and management decisions.^26^ We seek to build on these findings by investigating the potential impacts of new labels for melanoma in situ. To ensure relevance of our findings to end-users, we will test alternative labels for melanoma in situ that were chosen by our co-investigators representing clinicians, patients and the public. Alternative label(s) need to be acceptable to both patients and clinicians, and convey the low, but not zero, risk of future invasive melanoma. This study aims to explore whether using an alternative diagnostic label to communicate a hypothetical melanoma in situ diagnosis influences management choice and level of anxiety among Australian adults.

## Methods and analysis

### Study design

An online randomised study of Australian community members will be run, with participants randomised to receive one of the three hypothetical scenarios about the diagnosis of a melanoma in situ. Each group will be presented with a different diagnostic label, and we will survey participants about their preferred choices of management for that diagnosis, their level of anxiety about that diagnosis and their level of anxiety about their management choices.

This study is a between-subjects randomised online experiment. Following consent, eligible participants will be randomised 1:1:1 to ‘melanoma in situ’ (control), ‘low-risk melanocytic neoplasm’ (intervention label 1) and ‘low-risk melanocytic neoplasm, in situ’ (intervention label 2). The co-primary outcomes and secondary outcomes will be compared across randomised groups.

There will be an equal probability of being assigned to each of the three groups, and we expect approximately equal numbers per group. We will use Qualtrics survey software to randomly allocate participants into groups, present the scenarios, survey questions and collect data on the outcomes.^27^ Our participants’ flow diagram presents a summary of the randomisation of participants into the allocated control and intervention arms (figure 1).

**Figure 1 F1:**
[figure not shown]
Study Consolidated Standards of Reporting Trials flow diagram for participants. Participants’ selection inclusion criteria are age over 40 years, understanding written English and residing in Australia. Patients will be excluded if they have melanoma or do not provide consent.

### Eligibility criteria

Participants will be eligible if they are 40 years or older, understand written English and reside in Australia. Participants will be excluded if they have a history of melanoma (invasive or in situ).

### Recruitment and data collection

Participants will be recruited from the general Australian public through an independent social research company (Dynata), which has a panel of 600 000 participants whose demographic characteristics align closely with those of the national population. Dynata has a point system in which participants receive points after completing surveys. The points can then be used to redeem vouchers, cash or other rewards. Stratified sampling will be used, with quotas in place for gender (50% male, 50% female or other), age (25% for each of 40–29 years, 50–59 years, 60–69 years, 70 years or older, ±15% allowed for first three age groups and ±30% for oldest age group),^28^ education (50% high school or less, 50% more than high school, ±15% allowed) and State or Territory of residence (quotas proportionate to Australian population, ±5% allowed: New South Wales, 31.3%; Victoria, 25.6%; Queensland, 20.5%; South Australia, 6.9%; Western Australia, 10.9%; Tasmania, 2.1%; Northern Territory, 0.9%; and Australian Capital Territory 1.7%).^29^

Participants who agree to participate in the study will complete an online Qualtrics survey managed by the research team. Only eligible participants will proceed to the randomisation step. The survey will capture baseline data and characteristics of participants including socio-demographic details including their age, location, health literacy, and personal and family history of any cancer, and participant responses on outcome measures. The survey questions are presented in the online supplemental file.

All data will be collected via Qualtrics software and hosted on The University of Sydney secure server. Information will be de-identified, and we will not be able to link the survey back to participants. The non-identifiable data will be downloaded for analysis and stored within The University of Sydney’s Research Data Store.

### Determination of alternative labels to be tested

We undertook a targeted literature search in September 2023 by retrieving forward and backward citation searches of four key papers on the topic.^5 12 26 30^ We used the automated tool ‘Spider Cite’^31^ to identify records and Covidence to screen title, abstract and full texts.^32^ Of 593 unique records retrieved, we screened the full text of 27 and included seven papers describing nine alternative labels (see box 1).

Box 1Process to select alternative labels to melanoma in situ for testingIn the first-round surveys, clinician and patient/public co-investigators indicated their ranking the seven labels identified in the targeted literature search and two additional labels in order of preference. The potential alternative labels from the literature search were as follows: melanocytic neoplasm of low malignant potential (8, 24, 25), melanocytic neoplasm, atypical neoplasm (25), severe or high-grade melanocytic dysplasia, superficial atypical melanocytic proliferation of uncertain malignant significance (SAMPUS) (26–28), melanocytic tumour of uncertain malignant potential (MELTUMP) and melanocytoma (28). The two additional labels suggested by the research team were low-risk melanocytic neoplasm and low-risk melanocytic lesion.In the second-round surveys, co-investigators indicated their preferred ranking of the top three choices from round 1 and two new labels suggested in round 1: low-risk melanocytic neoplasm, low-risk melanocytic lesion and melanocytic neoplasm of low malignant potential, melanocytic intraepithelial neoplasia and in situ melanocytic neoplasm.In the third-round surveys, co-investigators indicated their preferred ranking of the top two choices from round 2 and three new labels suggested in round 2: in situ melanocytic neoplasm, low-risk melanocytic neoplasm, in situ melanocytic neoplasm, low risk, low-risk melanocytic neoplasm, in situ and dysplastic naevus.The two highest ranked labels, chosen as the alternative labels to test in the online experiment, were ‘*low-risk melanocytic neoplasm*’ and *‘low-risk melanocytic neoplasm, in-situ*’.

Using short online questionnaires implemented in Qualtrics,^27^ we then ran three rounds of surveys with the nine international clinician co-investigators (with expertise in dermatopathology, dermatology, surgical oncology, primary care and radiation oncology) and six patient/public co-investigators (two with lived experience of a melanoma diagnosis and four without a history of melanoma) to determine choice of alternative labels. This resulted in the final choice of two alternative labels that we will test in the online survey: *low-risk melanocytic neoplasm* and *low-risk melanocytic neoplasm, in situ*.

### Interventions

Participants will be randomised using Qualtrics randomisation software to receive one of the three hypothetical scenarios. They will not be blinded. In each scenario, the participant will be told that the results of their recent skin surgery indicate a particular diagnosis. Group 1 (the control group) will be told they have a *melanoma in situ*. Group 2 will be told that they have a *low-risk melanocytic neoplasm*. Group 3 will be told that they have a *low-risk melanocytic neoplasm, in situ*. We will not provide further explanation of what low risk means.

### Primary and secondary outcomes

Primary and secondary outcomes are described in table 1. The co-primary outcomes are (1) participant’s choice of surgical management option: no further surgery versus further surgery (to achieve pathology margins greater than 5 mm) and (2) follow-up management option: patient-led surveillance (self-skin examination with patient-initiated clinic visits) versus clinician-led surveillance (6 monthly routinely scheduled clinic visits).

**Table 1 T1:** Participant characteristics and outcome measures

Variable	Measure
**Participant characteristics**	
Melanoma risk	Melanoma risk prediction-based self-assessed risk factors^38^
General mood and well-being	WHO (Five) Well-Being Questionnaire^39^
Medical minimiser/maximiser	Single-Item Maximiser/Minimiser Elicitation Question (MM1)^40^
Health literacy	Single Item Literacy Screener (SILS)^41^
Melanoma worry	Direct choice between specified options, one choice possible
Self-efficacy	Generalised Self-Efficacy Scale (GSE)^42^
**Primary outcomes**	
Co-primary outcomes are choices for two management decisions. Choice of further surgery: No further surgery Further surgery to ensure margins>5 mm from lesion on pathology Choice of follow-up: Patient-led surveillance: self-monitoring with patient-initiated clinic visits as needed Clinician-led surveillance: 6 monthly routinely scheduled clinic visits	Direct choice between two management approaches for each co-primary outcomeChoice of further surgery and choice of follow-up
**Secondary outcomes**	
Diagnosis anxiety (feelings)	Single-question Visual Analogue Scale (0–6)^43 44^
Experiential perceived risk (vulnerability)	Single-question Visual Analogue Scale (0–6)^44^
Perceived lifetime absolute risk of invasive melanoma	Single-question Visual Analogue Scale (0–100)^44^
Perceived lifetime comparative risk of invasive melanoma	Single-question Visual Analogue Scale (0–6)^44^
Perceived lifetime risk of dying from melanoma	Single-question Visual Analogue Scale (0–100)
Management choice anxiety	Single-question Visual Analogue Scale (0–6)^43^
Open-text explanation of management choice	Free text (optional)

The first co-primary outcome on surgical management choice reflects recent retrospective analyses that have found that narrower margins are likely to be as safe as margins currently recommended in guidelines in small melanoma in situ.^33^ Indeed, very narrow histological clearance (≥1 mm) appears to be safe for melanoma in situ of the trunk and limbs.^34^ The new MPATH-Dx V2.0 melanocytic lesion classification scheme recommends that provided margins are not involved, and clinicians may consider not re-excising class II lesions—which includes melanoma in situ.^35^ The second co-primary outcome on follow-up management choice centres around patient-led surveillance (also called patient-initiated follow-up) as an alternative model of follow-up for cancer survivors to routinely schedule clinic appointments.^36^ Among people diagnosed and treated for early stage melanoma, patient-led surveillance is being evaluated in the MELanoma SELF surveillance (MEL-SELF) randomised controlled trial. Here, this model of care includes training in self-skin examination, digital technologies to record and take images of concerning lesions (using a mobile dermatoscope), online system for submitting images for remote review by a dermatologist and advice on whether urgent clinical review may be needed (teledermatology).^37^

Secondary outcomes are as follows: diagnosis anxiety, perceived lifetime risk of invasive melanoma, perceived lifetime risk of dying from melanoma, management choice anxiety and open-text explanation of management choices (free text input).

### Sample size

We estimated a sample size of 1668 participants with 556 participants per group in the study, which would provide 80% power (1 - β) to detect a pairwise difference in the proportion of choosing no further surgery and 89% power to detect a pairwise difference in the proportion in choosing patient-led surveillance as small as 10%.

The assumptions are 50% would choose no further surgery (most conservative assumption) and 35%^22^ would choose patient-led surveillance in the control label condition, a 5% dropout rate, α=0.05, the normal approximation to the binomial distribution and the standard formula for comparing proportions in independent equal-sized groups.

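### The stated 80% power for the surgery outcome does not follow from the stated inputs, which give about 90.5% (and about 91% for follow-up, against a stated 89%)

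*Protocol article*

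**What the plan says.** The abstract states: "The required sample size is 1668 people". The Sample size section repeats the number: "We estimated a sample size of 1668 participants with 556 participants per group in the study". It describes this as a size "which would provide 80% power (1 - β) to detect a pairwise difference in the proportion of choosing no further surgery and 89% power" for the follow-up outcome. The difference is printed only with the second figure: "89% power to detect a pairwise difference in the proportion in choosing patient-led surveillance as small as 10" per cent.

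The control-group rates are 50% for no further surgery and 35% for patient-led surveillance. The remaining assumptions are "a 5% dropout rate, α=0.05, the normal approximation to the binomial distribution and the standard formula for comparing proportions in independent equal-sized groups".

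The Analysis section sets all tests two-sided at 5% and plans pairwise comparisons across the three labels. Neither section mentions a divided or reduced α. The Sample size section does not say whether the difference from 35% is an increase or a decrease.

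**The concern.** Every input that a two-proportion power calculation needs is printed, so the two power figures should be reproducible. Two features suggest that they are not.

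- With more than 500 analysable per group, a 10-point difference from 50% should have power well above 80% at α=0.05.
- The control rates of 50% and 35% have similar binomial variances. For the same 10-point increase the two outcomes should therefore have nearly equal power, not figures 9 points apart.

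At stake is how a reader interprets a pairwise comparison that shows no difference. Such a result means something different in a design with about 91% power at α=0.05 than in one with about 81% power at a stricter α. The description of 1668 as the required number is affected in the same way.

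**Working it through.** **Inputs.** From Sample size: 556 per group, 5% dropout, control rates 50% and 35%, difference 10% (read as percentage points and as applying to both outcomes), α=0.05, normal approximation. From Analysis: two-sided tests. Analysable per group: 556 × 0.95 = 528.2, taken as 528.

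**Formula.** With Δ = |p1 − p2| and p̄ = (p1 + p2)/2,

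power = Φ( [Δ√n − z·√(2p̄(1−p̄))] / √(p1(1−p1) + p2(1−p2)) ), where z is the two-sided critical value.

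**Attempt to reproduce the plan's figures** (z = 1.960, √528 = 22.978, Δ√n = 2.2978):

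- Surgery, 50% vs 60%: (2.2978 − 1.960 × 0.7036)/0.7000 = 1.313, power **90.5%**. Stated: 80%.
- Follow-up, 35% vs 45%: (2.2978 − 1.960 × 0.6928)/0.6892 = 1.364, power **91.4%**. Stated: 89%.
- Follow-up, 35% vs 25%: (2.2978 − 1.960 × 0.6481)/0.6442 = 1.595, power **94.5%**. Stated: 89%.

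**Variants at α=0.05**

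| Variant | 50% vs 60% | 35% vs 45% |
|---|---|---|
| As stated, n = 528 | 90.5% | 91.4% |
| Dropout ignored, n = 556 | 91.9% | 92.7% |
| Continuity correction, n = 528 | 89.4% | 90.3% |
| One-sided, n = 528 | 94.8% | 95.4% |

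None of these brings surgery near 80%.

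**Sample size for 80% power, 50% vs 60%, α=0.05.** n = (1.960 × 0.7036 + 0.8416 × 0.7000)² / 0.10² = 387.3, so 388 analysable per group. Dividing by 0.95 gives 408 (from 387.3) or 409 (from 388), hence 1224 or 1227 in total. The planned 1668 is about 36% larger (1668/1224 = 1.36).

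**What might lie behind the figures**

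| Assumption changed, n = 528 | Surgery | Follow-up 35→45 | Follow-up 35→25 |
|---|---|---|---|
| α = 0.05/3 (z = 2.394) | 81.0% | 82.3% | 87.7% |
| Surgery difference 8.6 points, α = 0.05 | about 80% | 91.4% | 94.5% |

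At α = 0.05/3, 80% power for surgery needs (2.394 × 0.7036 + 0.8416 × 0.7000)² / 0.10² = 516.9, so 517 per group. That is 545 after dropout and 1635 in total, within 3% of 1668 (33/1668 = 2.0%).

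A loss of about 30% (1 − 388/556 = 0.302) would also bring surgery to 80%, but it contradicts the stated 5%.

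**The case against.** The strongest defence concerns the cause and the consequences, not the arithmetic.

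**The cause is open.** A reader might infer that N was set at an undisclosed stricter α. The document does not establish this. Grammatically, the 10% is attached only to the follow-up outcome, and no separate difference is printed for surgery. A surgery difference of about 8.6 points gives 80% at α=0.05. This stands: the stricter α is one plausible explanation, not a finding.

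**One reading comes close to both figures.** At α=0.05/3, with surgery rising from 50% to 60% and follow-up falling from 35% to 25%, power is 81.0% and 87.7%, within about 1.3 points of the stated 80% and 89%. The tests are two-sided and no direction is printed, so a fall is not excluded. This stands too. However, the Introduction's rationale, that a new label may allow less intensive surveillance, makes an increase the more natural hypothesis, and 0.05/3 is stated nowhere.

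**The 89% is a small miss.** For an increase it differs by 2.4 points from the stated formula, and by 1.3 points with a continuity correction that the text does not mention. It should not be given the same weight as the 80%.

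**The printed error rate is consistent.** Sample size and Analysis both say 5%, so a reader might infer a contradiction between them, but there is none on the page. One would arise only if an adjusted α is confirmed.

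None of this rescues the 80%. Any explanation needs an input that the paragraph either does not state or states differently.

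**Conclusion.** The stated power figures do not follow from the stated inputs. For surgery the discrepancy is material: 90.5% against a stated 80%. For follow-up it is minor if the difference is an increase (91.4% against 89%) and larger if it is a decrease (94.5%). The 1668 described as required exceeds the roughly 1224 to 1227 that 80% power for surgery needs at these inputs.

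This rests on reading the 10% as percentage points for both outcomes, on 5% loss in each group, and on the pooled-variance normal approximation. Changing the approximation does not alter the conclusion. Applying the 10% to follow-up only would, but then the surgery difference is missing from a paragraph that claims power for it.

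A reader might infer that the trial is too small. The opposite holds at the stated α: the design has more power than it claims, so the error is conservative. The cause remains unknown.

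**What to change.** Keep N=1668. Restate the Sample size paragraph with the α actually used, the difference for each outcome in percentage points, and the direction of the difference from 35%.

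- **If α=0.05 per comparison and the difference is 10 points for both outcomes:** report that 528 analysable per group give 90.5% power for surgery and 91.4% for follow-up (94.5% if the difference is a decrease). Drop the description of 1668 as the required number, or say what it is required for.
- **If an adjusted α was used:** name it and give the matching power. At 0.05/3 this is 81.0% for surgery, with 82.3% for an increase or 87.7% for a decrease in follow-up. Then align the 5% level in the Analysis section with it.
- **If the surgery difference was not 10 points:** print the one used, and correct the follow-up figure as well, since it remains 91.4% or 94.5% at α=0.05.

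The cost is one reworded paragraph, the matching phrase in the abstract and, only in the second case, one sentence in the Analysis section. Recruitment and data collection are unaffected.
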